## Abstract

**Introduction:**

Emerging adulthood is a phase in life that is associated with an increased risk to develop a variety of mental health disorders including anxiety and depression. However, less than 25% of university students receive professional help for their mental health reports. Internet-based cognitive behavioural therapy (iCBT) may entail useful interventions in a format that is attractive for university students. The aim of this study protocol is to test the effectiveness of a therapist-guided versus a computer-guided transdiagnostic iCBT programme with a main focus on anxiety and depression.

**Methods and analysis:**

University students with anxiety and/or depressive symptoms will be randomised to a (1) 7-week iCBT programme (excluding booster session) with therapist feedback, (2) the identical iCBT programme with computer feedback only or (3) care as usual. Participants in the care as usual condition are informed and referred to conventional care services and encouraged to seek the help they need. Primary outcome variables are self-reported levels of anxiety as measured with the General Anxiety Disorder-7 and self-reported levels of depression as measured with the Patient Health Questionnaire-9. Secondary outcomes include treatment adherence, client satisfaction, medical service use, substance use, quality of life and academic achievement. Assessments will take place at baseline (t1), midtreatment (t2), post-treatment (t3), at 6 months (t4) and 12 months (t5) postbaseline. Social anxiety and perfectionism are included as potentially important predictors of treatment outcome. Power calculations are based on a 3 (group) × 3 (measurement: pretreatment, midtreatment and post-treatment) interaction, resulting in an aimed sample of 276 participants. Data will be analysed based on intention-to-treat and per protocol samples using mixed linear models.

**Ethics and dissemination:**

The current study was approved by the Medical Ethics Review Committee (METC) of the Academic Medical Centre, Amsterdam, The Netherlands (number: NL64929.018.18). Results of this trial will be published in peer-reviewed journals.

**Trial registration number:**

NL7328.

Strength and limitations of this studyThe current study protocol describes a randomised controlled trial (RCT) focused on university students with anxiety and/or depressive symptoms.A transdiagnostic internet-based cognitive behavioural therapy programme, with either therapist guidance or computerised guidance, is compared with care as usual (three-arm RCT).The procedure of the trial is developed to make it easily accessible and anonymous, and the full procedure is online.The therapists are not fully blinded to the treatment condition.The post-treatment outcomes rely on self-reports of the participants.

## Background

Emerging adulthood is a crucial stage in life that includes the transition from the teenage years to full-fledged adulthood (18–25 years). It is a phase during which many young adults attend university to receive education and training to obtain a degree that will be the basis for their adult working life.^1^ It is also the phase that is associated with an increased risk of developing a variety of mental health disorders such as anxiety and depression,^2–4^ whereby comorbidity is the rule rather than the exception.^5^ Recent studies found that between 16% and 46% of all students suffer from mental health disorders.^2 6^ Moreover, these problems have been associated with poorer academic performance, academic dropout, decreased labour market functioning and poorer social and health outcomes.^6–10^ Early detection and effective intervention are, thus, crucial with regard to the long-term prognosis of mental disorders, especially as untreated mental disorders have a mean duration between 4 and 23 years.^11^

Online treatment programmes may be useful as an intervention in a format that is particularly attractive for university students, given the fact that less than 25% of students with mental health problems use available face-to-face services.^12^ University students might avoid help due to several reasons, including fear of stigmatisation, lack of perceived urgency, preference to deal with it themselves, threat to identity formation and goal setting and/or scepticism regarding treatment effectiveness.^13 14^ This group may be more likely to seek help if an effective, more flexible, easily accessible and anonymous intervention strategy is provided. A scoping review by Boydell *et al*^15^ concluded that internet therapies have (untapped) potential to provide better information about mental health and may improve the cost efficacy of mental health services. Moreover, their study indicated that young people, in general, prefer eHealth treatments relative to face-to-face services.

Several studies demonstrated that the effectiveness of guided internet-based cognitive behavioural therapy (iCBT) programmes for anxiety and depression is comparable to conventional (face-to-face) CBT (for meta-analyses, see Carlbring *et al* and Cuijpers *et al*^16 17^). There is also some evidence for the effectiveness of internet interventions for young adults and university student populations with various mental health problems, including depression, anxiety, eating disorders, stress, alcohol and sleep problems^18–22^. For example, a recent meta-analysis^20^ focused on university students with mental problems, who self-selected a psychological online intervention (guided/unguided). They found small intervention effects for depression (*g*=0.18, 95% CI (0.08 to 0.27) and anxiety (*g*=0.27, 95% CI (0.13 to 0.40)) in university students. It should be noted, however, that the effects on anxiety were not significant anymore after adjusting for publication bias. Harrer and colleagues^20^ concluded that clearly more research is needed to explore ways to increase treatment effectiveness for university students and to study predictors of treatment outcome.

The current study includes a group of university students and focuses on two of the most common mental disorders in this group, namely, anxiety and depression.^2^ As comorbidity is high, we will use a transdiagnostic iCBT intervention, which has the advantage to target both disorders at the same time and thereby might increase treatment effectiveness (for a systemic review and meta-analysis, see Newby *et al*
23). Moreover, iCBT programmes can be provided with or without additional personal guidance. Guidance usually implies written or verbal feedback by the therapist to the patient’s homework assignments and other forms of (safe) communication (eg, chat, telephone) within an online environment with varying degrees of interactive features.^24^ Both approaches (with and without personal guidance) have shown to be efficacious, although programmes with (therapist) guidance generally report a higher effect size (for meta-analyses, see Cuijpers *et al* and Richards and Richardson 17 25), even though it should be noted that a recent meta-analysis^20^ found no difference between personal or no personal guidance. To date, little is known about the effectiveness for therapist-guided versus a computer-guided version of the same intervention tested *within* the same study when applied to a university student sample with mental health concerns^20 26 27^. This could also have important health economic implications considering the additional cost of human support. Therefore, the current study tests this transdiagnostic iCBT for anxiety and depression in three groups; a therapist-guided online self-help version, a computer-guided version of the same programme and care as usual (CAU). Primary outcomes were anxiety and depression; secondary measures were included to evaluate treatment adherence and satisfaction, academic achievement and medical service use.

Internet-based programmes, either therapist-guided with personal feedback or computer-guided with automated feedback, might suit some individuals better than others. It is important to focus on possible treatment predictors (eg, including baseline symptoms severity, gender, personality factors and comorbidity), as this may help us understand more about the heterogeneity of treatment response.^20 28^ Specially, a recent meta-analysis^20^ found limited effectiveness on anxiety in university students in their meta-analysis. The current study will focus on the possible role of social anxiety and perfectionism, as there is some evidence that adults and children with social anxiety might benefit less from general CBT programmes (for meta-analyses, see Hudson *et al* and Norton and Price^29 30^). Likewise, self-critical perfectionism is a transdiagnostic personality factor that is generally associated with worse treatment outcome, including CBT.^31^ Importantly, individuals with self-critical perfectionism have poorer social relationships, which in turn negatively impacts therapeutic progress.^32^

The aim of this study is to test the effectiveness of a therapist-guided versus a computer-guided transdiagnostic iCBT programme with a focus on anxiety and depression. Based on previous studies in the general population,^17^ we hypothesise that the therapist-guided iCBT and computer-guided iCBT conditions are both significantly more effective than CAU. In addition, we expect that the therapist-guided iCBT condition is significantly more effective than the computer-guided iCBT condition; an effect we expect to be mediated by higher treatment adherence.

## Methods

### Study design

The current study includes a randomised controlled trial (RCT) design with three arms, consisting of (1) a therapist-guided transdiagnostic iCBT programme with personalised feedback, (2) a computer-guided version of the same CBT programme with automated feedback and (3) CAU. We used the Standard Protocol Items: Recommendations for Interventional Trials reporting guidelines for this study^33^; see online supplemental appendix A.

10.1136/bmjopen-2021-049554.supp1Supplementary data

### Eligibility criteria

All students scoring 16 or higher on the Center for Epidemiological Studies Depression Scale (CES-D)^34^ and/or a score of 5 or higher on the General Anxiety Disorder-7 (GAD-7)^35^ were included in the study. There is no higher end cut-off. Participants are excluded from the study if they (1) are younger than 16 years of age, (2) currently receive psychological treatment (as described by the American Psychological Association (APA) dictionary) for anxiety and/or depression, (3) do not have access to a stable internet connection for the next 2 months, (4) if they meet the diagnostic criteria for (recent or current) psychotic disorder according to the Mini International Neuropsychiatric Interview (MINI),^36^ (5) if they are at active high risk for suicide based on the MINI and (6) if they do not give informed consent. Participants meeting exclusion criteria 4 and/or 5 are referred to local healthcare facilities.

### Recruitment

All participants were recruited at the University of Amsterdam (UvA), The Netherlands. The UvA is a public research university located in Amsterdam. It is one of the largest research universities in Europe with 31 186 students enrolled in 2018 and includes seven faculties: Humanities, Social and Behavioural Sciences, Economics and Business, Science, Law, Medicine and Dentistry. Recruitment for the study is done in two phases: a first broad screening phase for all university students studying at the UvA and a second more specific screening of eligible students who showed interest to participate. In the first broad screening phase, all students enrolled at the UvA receive an invitation via email that are sent centrally from the study platform. In addition, study advisors and study counsellors of the UvA are informed about the study and are asked to refer students who are interested in participating in the study to the research team, so that they can be invited by email.

This first broad-screening invitation email contains general information about the study and a unique link to fill out the screening questionnaire. This screening questionnaire takes approximately 20 min to complete and also includes other questionnaires related to the mental health of university students. This screening questionnaire was developed in collaboration with other universities to collect multicentre data. Participants who click on the invitation link are referred to the project platform. Here, they find an information letter and are asked to give online informed consent to the research team. This information letter explicitly states that participation is voluntary and that participants can withdraw at any time without consequences. Next, participants are asked to create an account after which they are directed to the screening questionnaire. Following the original invitation, two reminder emails are sent 1 and 2 weeks after the first invitation. As the study runs for three academic years (2019–2021), participants are asked at the beginning of the screening if they consent to being invited again later. Moreover, participants can also indicate that they do not want to receive any emails again.

In the second more specific screening phase, university students who score above the cut-off on either anxiety (GAD-7) and/or depressive symptoms (CES-D) receive an email with an online information brochure and informed consent document^34 35^; see online supplemental appendix B. After informed consent is given by the participant, they are called by a trained clinical research assistant to check all of the inclusion and exclusion criteria. A telephonic diagnostic interview (MINI) 36 is administered to establish possible diagnoses with respect to mood and anxiety disorders, bipolar disorder, psychosis and suicidal ideation (not fulfilling the criteria for an anxiety and/or mood disorder is not an exclusion criterion).

10.1136/bmjopen-2021-049554.supp2Supplementary data

### Randomisation, blinding and treatment allocation

Participants are randomly assigned to either the therapist-guided online intervention, the computer-guided online intervention or CAU (control) condition (1:1:1 allocation ratio) directly following the baseline measurement. Randomisation is stratified by gender and anxiety and/or depressive symptoms (based on the cut-off scores on the screening questionnaire). Sequence generation is based on computer-generated random numbers and are allocated by an automatic system.

Due to the nature of the intervention, participants and researchers cannot be completely blinded to the assigned treatment condition, though note that the measurements in the intervention are blinded. Researchers are aware of the participants’ condition because they provide participants with feedback in the therapist-guided condition. In the computer-guided condition, feedback is automatically generated by the system, but therapists do send reminders to this group as part of the intervention.

### Intervention

The online transdiagnostic intervention that is used in this study, ‘ICare Prevent’, was originally developed by Weisel *et al*^37^ for the general German-speaking population and translated and adapted by Bolinski *et al*^38^ and Karyotaki *et al*^39^ for a Dutch undergraduate student population into Dutch and English. The intervention was based on other effective protocols^40–43^ and can be seen as a variant of an iCBT protocol for which several studies have proven its effectiveness. The intervention is provided to the participants through the eHealth platform Minddistrict. This platform enables researchers and healthcare providers to provide digital therapy to their participants and patients. On this platform, e-coaches create a personal account for each participant directly following the baseline assessment and randomisation. Once the personal account has been created, the participant receives an email with information how to activate the account. Once the account is activated, the participant can start with the intervention. The platform monitors the progress of the participants, e-coaches provide support for the participants in the therapist-guided treatment condition and respond to questions from the participants with the messaging function. Data processing and storage are in accordance with the ISO 27000 and NEN 7510 norms. A data processing agreement that complies with the European General Data Protection Regulation (GDPR) has been signed between eHealth provider Minddistrict and the UvA.

The intervention is based on basic cognitive behavioural therapy principles for anxiety and depression with components of psychoeducation, including online exercises and home assignments. The intervention consists of seven regular sessions (45–60 min per session) and one booster session (4 weeks after the completion of the last session). From the second session onwards, participants are able to follow eight additional optional modules based on their personal needs, including sleep, perfectionism, alcohol use, reduce rumination, self-worth, acceptance, appreciations and rest and relaxation. They can decide to choose one additional module per session, and they are free to repeat this module or choose other modules in later sessions. In sessions 5 and 6, users decide to follow either content directed at changing negative cognitions or exposure to feared situations. Participants are free to decide when they would like to start a treatment session and if they want to do an additional module, but it is advised to do at least one and no more than two treatment sessions per week. For a full description of the intervention, see Karyotaki *et al*.^39^

#### Therapist-guided intervention versus computer-guided intervention

During the intervention, participants in both conditions receive online support in the form of messages or notifications in the messaging function (e-mails). In both conditions, participants receive up to 3 weekly reminders via the messaging function when they are inactive. Moreover, participants in both conditions can use the messaging function to ask questions. All participants can ask technical or usability related questions. There is one key difference between the two conditions: Participants in the computer-guided iCBT condition receive automatically generated feedback messages (see online supplemental appendix C for an example). In contrast, in the therapist-guided condition, the e-coaches (trained psychologists on minimal Bachelor (BA) level) provide detailed feedback based on participants’ output of the sessions, and this feedback is displayed at the bottom of the session they completed (see Appendix C for an example). The coach spends approximately 30 min on providing feedback per session and intends to give feedback within five working days after the session is completed by the participant. During the trial, training and weekly supervision for the e-coaches who are guiding the participants are provided by a licensed mental healthcare psychologist.

10.1136/bmjopen-2021-049554.supp3Supplementary data

### Care as usual

Participants in the CAU condition are informed and referred to conventional care services and encouraged to seek the help they need. Medical services used by the participants during the RCT are monitored through self-report questions at t3, t4 and t5. Participants in the CAU condition are assessed at the same time points as the two intervention conditions including the weekly questionnaires during the first 7 weeks.

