### Suicide risk monitoring

All participants receive an information brochure with all relevant contact information as part of the information package they receive prior to the study. In addition, the brief version of the PHQ-9, the PHQ-4^44^ is administered before each treatment session or weekly via email (CAU). Suicide risk is monitored with the help of a suicide risk protocol that was created specifically for this study ([name] *et al Suicide protocol)*. Suicide risk is monitored using item 3 (‘feeling down, depressed or hopeless’) of the PHQ-4 and item 9 (‘thought that you would be better off dead, or of hurting yourself’) of the Beck Depression Inventory scale.^45^ If deemed necessary, participants are called and referred to appropriate services, including their General Practitioner (GP) or 113zelfmoordpreventie (online platform for suicide prevention). In addition, the participant also receives a pop-up message on the questionnaire page with relevant contact information right after filling in the questionnaire (ie, where they can find help if needed with relevant contact information).

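### Medical service use is a secondary outcome with no baseline measurement, so continuing care cannot be separated from new care; and because only CAU includes routine referral, higher use in CAU should not be read as care spared by iCBT (minor)

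*Protocol article*

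**What the plan says.** The abstract lists the outcome: "Secondary outcomes include treatment adherence, client satisfaction, medical service use, substance use, quality of life and academic achievement". The Secondary outcomes section says it is measured with two TiC-P items. One is the frequency of contact with conventional services, with the GP, study advisor, psychologist and medical specialist as examples. The other is medication use over the treatment period.

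On timing, the Care as usual section states: "Medical services used by the participants during the RCT are monitored through self-report questions at t3, t4 and t5". Table 1 agrees: the TiC-P row is marked at t3, t4 and t5 only. Alcohol use, drug use, quality of life and both academic achievement measures have a t1 mark.

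On care at entry, the relevant exclusion is for those who "currently receive psychological treatment (as described by the American Psychological Association (APA) dictionary) for anxiety and/or depression". The other five criteria concern age, internet access, psychotic disorder, suicide risk and consent.

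On referral, the comparator is defined as follows: "Participants in the CAU condition are informed and referred to conventional care services and encouraged to seek the help they need". No routine referral is described for the two iCBT arms. Under Suicide risk monitoring, however, "All participants receive an information brochure with all relevant contact information as part of the information package they receive prior to the study", and any participant may be called and referred when risk monitoring calls for it.

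**The concern.** There are two separate issues.

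The first is the missing baseline. A student who already takes medication or sees a GP or specialist is not excluded by the listed criteria. At t3 that student's contacts or medication look the same as those of a student who started after randomisation. The trial then cannot show how much of this background care each arm carried in, and cannot adjust later service use for earlier use.

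The second concerns interpretation. Sending people to conventional services is what the CAU condition consists of, and contact with such services is also counted as an outcome. If CAU shows more contacts, a reader could conclude that iCBT reduces the need for care, when part of the difference may come from the referral itself. The Background says "less than 25% of students with mental health problems use available face-to-face services", which makes it plausible that prompting could move use, but gives no figure for how far.

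**Working it through.** The plan states no figure on this point, so there is none to reproduce. The check is a comparison of sections, followed by an illustration of size.

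**Which care is ambiguous without a t1 measurement**

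| Care counted by the TiC-P items | Covered by an exclusion at entry? | New after entry? |
|---|---|---|
| Psychological treatment for anxiety or depression | Yes, if current | Yes, apart from misreporting |
| Therapy for other problems | No | Cannot be told |
| GP, specialist, study-advisor contact | No | Cannot be told |
| Medication | Not mentioned | Cannot be told |

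That medication is permitted follows from its absence from the exclusion list; no sentence says so. Randomisation is stratified by gender and by anxiety and/or depressive symptoms, so stratification does not balance background care either.

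**How large a chance imbalance could go unseen**

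Inputs: 92 per arm (Sample size calculation). With the plan's 35% dropout, 92 × 0.65 ≈ 60 per arm remain. The share p with ongoing care at entry is not given; 5% to 30% is assumed.

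The 95% range of the difference between two arms is ±1.96 × √(2p(1−p)/n).

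| p (assumed) | n = 92 | n = 60 |
|---|---|---|
| 5% | ±6.3 points | ±7.8 points |
| 10% | ±8.7 | ±10.7 |
| 20% | ±11.6 | ±14.3 |
| 30% | ±13.2 | ±16.4 |

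**What a baseline covariate would be worth**

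In a linear model, adjusting for a baseline that correlates r with the outcome multiplies the effective sample size by about 1/(1−r²). The value of r is assumed:

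- r = 0.3: 1/0.91 = 1.10
- r = 0.5: 1/0.75 = 1.33
- r = 0.7: 1/0.51 = 1.96

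At 60 per arm this is worth about 66, 80 and 118 per arm respectively. For a count outcome it is only a guide.

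**Who is prompted to use care**

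Contact information goes to all arms. Risk-triggered referral can occur in any arm. Routine referral with encouragement is described for CAU only. The therapist-guided and computer-guided arms are therefore alike in referral, while each differs from CAU.

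**The case against.** The strongest reply starts from randomisation. Allocation is 1:1:1 directly after baseline, so prior care is balanced in expectation and the missing baseline creates no arm difference. This stands. A reader might infer that a difference is built in by the assessment schedule, but the documents do not support that: a t1 measurement would leave the referral contrast exactly as it is.

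Second, the care that matters most for the primary outcomes is largely unambiguous. A trained assistant checks all criteria by telephone, and current psychological treatment for anxiety or depression excludes. Treatment of that kind reported later is new, apart from misreporting. This also stands, so it would be wrong to say that new care in general cannot be identified.

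Third, Table 1 does not list everything collected at entry (it omits the MINI and the demographics), so background treatment may be recorded elsewhere. That is possible, but both the text and the table schedule the service-use items from t3 only.

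Fourth, no hypothesis predicts that iCBT spares care, and the Background's health-economic remark concerns the added cost of human support. The abstract and the Care as usual section also disclose what CAU consists of. All this is correct. The interpretive point is a caution about a named outcome; the plan announces no faulty inference.

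Finally, it is tempting to put a size on the referral effect. With 25% use unprompted and 40% to 50% after referral, a two-proportion comparison would be significant at two-sided 0.05 with probability about 0.60 to 0.95 at 92 per arm, or 0.43 to 0.83 at 60 after dropout. These figures are not evidence. The uptake is invented, the 25% describes students with mental health problems generally, and the TiC-P item counts contacts, not yes/no use.

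**Conclusion.** The point holds in a limited form. For medication, for GP, specialist and study-advisor contact, and for therapy for other problems, the plan cannot separate continuing from new use, cannot show chance imbalance and has no baseline for adjustment. The cost is precision and description, with no bias in expectation. Under the assumed 5% to 30% with ongoing care, the unseen imbalance could reach about 6 to 13 points at 92 per arm and 8 to 16 points at 60. The precision forgone is a factor of about 1.10 to 1.96 if baseline and later use correlate at 0.3 to 0.7, also an assumption.

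Separately, higher service use in CAU partly reflects the allocated condition and should not be read as care spared by iCBT. The documents do not allow the size of that effect to be stated. This is a minor point about one secondary outcome, and the validity of the GAD-7 and PHQ-9 comparison does not depend on it.

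**What to change.** 1. Add the two TiC-P items at t1 with a fixed look-back. Use them as baseline covariates for service use and to describe background care by arm.
2. For participants already enrolled, ask at their next assessment whether the reported care or medication began before randomisation. The Recruitment section describes inclusion over 2019–2021, so a new t1 item reaches only later entrants.
3. Interpret iCBT-versus-CAU service use as a description of care received under the comparator. Keep therapist-guided versus computer-guided as an outcome comparison, since routine referral does not differ between those arms.

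The cost is two more self-report items in an existing questionnaire and incomplete baseline data for those already enrolled. The retrospective question also depends on recall. A claim about care use against CAU is given up.
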